### Compliance

To assess how well participants adhere to their diets, their dietary intakes will be recorded once every 2 weeks in the first phase and every 4 weeks in the second phase by telephone interview. A sample of dietary recall format is provided in Supplementary file, section C. In total, participants are going to complete 12 dietary records (six in the first phase and six in the second phase). Participants will be asked to report their dietary intakes using household measures in order to complete the dietary recalls. Then, we will convert household measures to grams using the booklets provided. Participants’ total dietary intakes will be assessed using the average of all dietary recalls taken over the duration of the intervention. Total energy intake, macronutrients, and micronutrients will be computed from the dietary recalls using Nutritionist-IV software (First Databank, San Bruno, CA, USA) modified for Iranian dishes. We will also send text messages and make phone calls to participants throughout the study to increase compliance and prevent forgetfulness of diet principles.

### Intervention safety

There have been no serious side effects associated with moderate carbohydrate restriction diets. To investigate any potential side effects, we will ask participants to report any changes during the study period concurrent with their dietary assessment via phone interview.

### Assessment of variables

A standard questionnaire will be used to collect data on participants’ age, ethnic origin, marital status, educational level, disease history, family history of disease, medication use, and history of COVID-19 and type of vaccination. We will also measure primary outcomes including serum lipid profile concentrations, fecal bacterial load, and glucose levels, as well as secondary outcomes including anthropometric measurements and blood pressure at the beginning of the study, end of the phase I (3 months), and end of the phase II (6 months).

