## Abstract

**Background:**

Metabolic syndrome (MetS) is a group of risk factors that increase the risk of death and a variety of chronic diseases. Recent studies have indicated that the imbalance of gut microbiota might contribute to development and progression of metabolic syndrome. Carbohydrate restriction in the diet has been proven to be one of the most effective methods in the management of metabolic syndrome, even in the absence of weight loss. However, no study has examined the effects of a carbohydrate-restricted diet on gut microbiota composition in metabolic syndrome patients. Thus, we will examine the effects of a “moderately restricted carbohydrate (MRC)” diet on gut microbiota, insulin resistance, and components of MetS among Iranian women. In addition, the stability of changes in dependent variables, including gut microbiota, will also be assessed.

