### Sample size calculation

Using a type I error of 5% (*α* = 0.05) and a type II error of 20% (*β* = 0.20, power = 80%), and serum HDL-C concentrations as the key variable, the sample size in this study was calculated using the following formula, which has been proposed for parallel clinical trials:$$n=\frac{2\left[{\left({\textrm{Z}}_{1-\frac{\alpha }{2}}+{\textrm{Z}}_{1-\beta}\right)}^2\times {\upsigma}^2\right]}{{\textrm{d}}^2}$$

*n* = sample size for each group.

*σ* = The variance (SD) for mean HDL-C concentrations was as 3.5, which was calculated using the average SDs reported for serum HDL-C in Rajaie et al. study [35].

*d* = The minimal clinically important difference for HDL-C was set at 2.5, based on previous research [38].

Overall, using this formula and assuming a 10% drop-out rate in each group, we will require a sample size of 35 subjects in each group.

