### Biochemical assessments

A blood sample will be taken from each patient’s venous blood at the study baseline, end of the first phase (after 3 months), and end of the second phase of the study (after 9 months) following 12 h of fasting. We will use a portion of the blood sample to evaluate glucose levels and lipid profile. The remaining serum will be kept at – 80 °C until it is further analyzed for insulin levels. Plasma glucose and lipid profile concentrations (TC, HDL, LDL, and TG) will be determined via an enzymatic colorimetric method using commercial kits. Finally, the serum insulin concentrations will be examined using electrochemiluminescence (ECL) method. We also will determine insulin resistance (HOMA-IR) and quantitative insulin-sensitivity check index (QUICKI) formulas.

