### Stool samples and gut microbiota assessment

A 10-g stool sample will be collected from each participant at study baseline, 3 months after intervention, and 6 months after the end of intervention using a stool specimen collection kit that will be brought to the clinic in ice packs within 4 h. Until fecal microbial analysis, stool samples will be frozen at – 80 °C in the laboratory. To minimize changes in the quantity of fecal bacteria, we will collect stool samples in one of three ways: first, we will invite patients to visit the laboratory on the day of fecal sampling. The lab will be equipped with all of the necessary equipment to collect fecal samples. The second method requires the patient to transport the sample to the laboratory within 4 h of their sampling. Finally, if the patient is unable to complete any of the prior approaches, they should contact the study researchers, who will collect their sample at their home and transfer it within 4 h to the lab.

DNA extraction from 200 mg of frozen stool samples will be done using a FavorPrep Stool DNA Isolation Mini Kit (Favorgen Biotech Corp., Taiwan) according to the manufacturer’s instructions. The extracted bacterial DNA purity and concentration will be determined by Nanodrop spectrophotometer (Thermo Scientific NanoDrop, USA). All the extracted DNAs will be stored at − 20 °C freezer until further analysis. Additionally, the quantity of fecal bacteria, including Firmicutes, Bacteroidetes, *Bifidobacteria*, *Lactobacillus*, *Clostridium*, *Prevotella*, *Bacteroidetes*, and *Akkermansia muciniphila*, will be determined using a quantitative real-time polymerase chain reaction (qRT-PCR) in duplicate. We selected the taxa based on their association with metabolic syndrome and their ability to balance the gut microbiota [39, 40]. Specific primers targeting the bacterial 16S rRNA genes blasted in NCBI will be used in the current study. Each reaction mixture is composed of SYBR Premix Ex Taq II (Takara, China), the specific forward and reverse primers, and a DNA template. The thermal cycling conditions will be as follows: an initial DNA denaturation step at 95 °C for 1 min, 40 cycles of denaturation at 95 °C for 5 s, primer annealing at 55 °C for 30 s, and extension at 72 °C for 30 s. Finally, in order to confirm the specificity of the amplification products, melting curve analysis will be performed by slowly cooling the PCRs from 95 °C to 60 °C.

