### Statistical analysis

All statistical analyses will be carried out using the SPSS software version 25 (SPSS Inc., Chicago, IL, USA). For addressing non-adherence, the intention-to-treat (ITT) analysis will be applied [41]. Moreover, we will apply the last observation carried forward method (LOCF) to handle missing values [42]. In order to determine the normal distribution of variables, we will use the Kolmogorov-Smirnov test, histogram, and Q-Q plot. We will log transform (ln) the data, if necessary, to achieve normal distribution. Data will be presented as mean ± standard deviation (SD) for continuous variables and as percentages for categorical variables. Chi-square test and independent samples *t*-test will be used for comparing continuous and categorical variables between the two groups, respectively. We also will use the paired-sample *t* test for within-group comparisons. Repeated measures analysis of variance will be employed to determine the impact of the intervention on the outcome variables. These analyses will examine the effects of the intervention, time, and the interaction between time and intervention. Any potential differences in baseline levels of outcome variables, dietary intakes, and physical activity will be controlled in these analyses. Statistical significance will be defined as *P* values less than 0.05.

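### Several co-equal primary outcomes are each judged at P<0.05, but the sample size covers HDL-C alone, so the primary claim has an inflated false-positive risk and the microbiota aim has no stated power

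*Protocol article*

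**What the plan says.** The Assessment of variables section of the protocol article gives "primary outcomes including serum lipid profile concentrations, fecal bacterial load, and glucose levels", measured at baseline and at the end of each phase. Anthropometry and blood pressure are secondary.

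Two later sections show what these groups contain. Biochemical assessments refers to "Plasma glucose and lipid profile concentrations (TC, HDL, LDL, and TG" in brackets, which is four lipids plus glucose. Stool samples and gut microbiota assessment describes "the quantity of fecal bacteria, including Firmicutes, Bacteroidetes" and further taxa by PCR. That list has eight names, with Bacteroidetes printed twice, so seven are distinct.

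The Sample size calculation section uses "serum HDL-C concentrations as the key variable", with a two-sided 5% type I error and 80% power, and arrives at 35 per group. No SD, effect size or power is given for any bacterial outcome.

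The Statistical analysis section plans repeated-measures analysis of variance with group, time and interaction effects, controlling for baseline differences. It ends with a single rule: "Statistical significance will be defined as" a P value below 0.05.

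The abstract puts microbiota first among the effects to be examined: "diet on gut microbiota, insulin resistance, and components of MetS among Iranian women". Aim (i) at the end of the Background section has the same order.

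**The concern.** Three parts of the article point to three different lead outcomes. The sample size points to HDL-C, the outcome list to lipids, bacteria and glucose jointly, and the aims to microbiota. Which outcome is primary is a protocol decision, and the article has made it inconsistently.

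Two things are at stake. First, with several outcomes of equal rank each tested at 0.05, any one of them can be reported as a positive primary result, so the error rate for the primary claim is well above the 5% used in the sample size. Second, nothing tells the reader what size of microbiota change the trial can detect, although that is its headline question.

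**Working it through.** **1. The planned sample size.** Inputs from the Sample size calculation section: two-sided α = 0.05, power 80%, σ = 3.5, d = 2.5, dropout 10%. The text labels 3.5 both a variance and an SD. Only the SD reading reproduces the stated figure; as a variance it would give 9 per group.

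n = 2(1.960 + 0.842)² × 3.5² / 2.5² = 30.77, so 31 per group. After dropout, 31/0.9 = 34.4, so 35 per group. The planned figure reproduces. The HDL-C effect is 2.5/3.5 = 0.714 SD, and power with 31 per arm is 80% by this formula (79% by the exact t-test).

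**2. The number of primary variables.**
- TC, HDL-C, LDL-C, TG: 4
- Glucose: 1
- Distinct taxa: 7
- Total: 12 (13 if the repeated name stands for another taxon)
- If fecal bacterial load is one variable: 4 + 1 + 1 = 6

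**3. Chance of at least one false-positive primary result.** This assumes no true difference on any outcome, and one between-arm test per outcome at one time point. For k independent tests it is 1 − 0.95^k. The correlated cases are simulated with equally correlated two-sided z-tests (400,000 draws). The correlations are assumptions, because the article gives none.

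| Outcomes | Correlation | Chance of at least one P<0.05 |
|---|---|---|
| 12 | 0 | 46.0% |
| 13 | 0 | 48.7% |
| 12 | 0.3 | 40% |
| 12 | 0.5 | 32% |
| 12 | 0.7 | 23% |
| 6 | 0 | 26.5% |

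**4. What the design can detect for one taxon.** With 31 completers per arm, two-sided 0.05 and 80% power:
- Normal approximation: (1.960 + 0.842) × √(2/31) = 0.71 SD
- Exact t-test: 0.72 SD
- With baseline adjustment, multiply by √(1 − ρ²), where ρ is an assumed correlation between baseline and follow-up. For ρ = 0.5, 0.723 × 0.866 = 0.63 SD. For ρ = 0.7, 0.723 × 0.714 = 0.52 SD.

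For a shift of 0.5 SD, the unadjusted t-test has 49% power. None of these figures allows for testing several taxa.

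**5. What it would cost to keep all 12 as primary.** Bonferroni gives 0.05/12 = 0.0042 per test. Power for the planned HDL-C effect at 31 per arm falls to 44% (t-test; 48% by the normal formula). Restoring 80% would need 54 completers per arm. That is 54/0.9 = 60 per arm, or 120 in total against the planned 70.

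**The case against.** **The count and the independence assumption.** Lipids come from one blood sample and taxa from one stool sample, so independence is a worst case. A reader might infer that a false-positive primary result is close to a coin flip; the documents do not support that as a headline, since the figure drops to 32–40% at moderate correlation. The count of 12 is also a reading. Six is possible, although the stool section describes only taxon-specific quantities and no total-load assay. These points lower the figure, but the 6-outcome reading still gives about five times the nominal 5%.

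**Repeated visits.** A reader might double the tests for 3 and 9 months and reach 71–74% (1 − 0.95^24 and 1 − 0.95^26). That treats two visits by the same women as independent, and the article plans a repeated-measures model, not two separate primary tests. The figure should not be used. Three months is also the implied main time point, because afterwards both arms follow the same maintenance diet, but the article does not label it as such.

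**Microbiota power.** The 0.72 SD figure ignores the baseline control that the article states, hence the adjusted range. A reader might infer that a null microbiota result could not be interpreted. That goes too far, since a confidence interval is informative at any sample size.

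**The unseen analysis plan.** A multiplicity method is commonly left to the SAP, and its absence here is not the finding. The mismatch between the stated primary set and the one sized variable remains. A SAP rule that split alpha would reduce the power the sample size was built on.

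**Minor points.** The repeated taxon looks like a slip. Insulin resistance is named in neither outcome list, but both lists are open and HOMA-IR and QUICKI are planned. Both are matters of wording.

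**The choice of HDL-C.** An ordered hierarchy that kept a microbiota primary would also control error. It is a legitimate alternative, but the present sample size offers no justification for it.

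**Conclusion.** The point holds. The article names several primary outcomes of equal rank, judges each at P<0.05 and sizes only one. The HDL-C calculation is correct; the fault is in how the primary outcome is defined.

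If the diets do not differ, the risk of at least one false-positive primary result at one time point runs from about 26% (6 independent outcomes) through 32–40% (12 outcomes, assumed correlation 0.5–0.3) to at most about 46% (12 independent outcomes). A correlation as high as 0.7 among the 12 would bring it to 23%.

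The leading microbiota aim has no stated power. With 31 completers per arm, 80% power per taxon is reached only at about 0.72 SD unadjusted, or 0.63 to 0.52 SD with baseline adjustment at assumed correlations of 0.5 to 0.7. This should be settled before the results are analysed, because it decides what the trial may claim.

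**What to change.** By a dated amendment to the protocol and the registry entry, made before any look at outcome data:

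1. Name the between-arm difference in HDL-C at 3 months as the single primary outcome, tested at two-sided 0.05. This is what the sample size supports.
2. Make the named taxa one key-secondary family, with Holm or Benjamini-Hochberg control at 5%, and correct the repeated name so that the family is fixed.
3. Report the other lipids, glucose, HOMA-IR and QUICKI, anthropometry, blood pressure and all 9-month results as secondary estimates with confidence intervals.
4. State the microbiota shift the trial can detect, with its assumptions: completers per arm, assumed baseline correlation, and whether the figure allows for several taxa.

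No extra participants are needed; 35 per arm stands. The cost is fewer claims of significance and a formally secondary role for microbiota. Because the trial is registered and has been recruiting since December 2021, this is a substantive change, and its timing relative to outcome data must be documented.

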### Biochemical assessments

A blood sample will be taken from each patient’s venous blood at the study baseline, end of the first phase (after 3 months), and end of the second phase of the study (after 9 months) following 12 h of fasting. We will use a portion of the blood sample to evaluate glucose levels and lipid profile. The remaining serum will be kept at – 80 °C until it is further analyzed for insulin levels. Plasma glucose and lipid profile concentrations (TC, HDL, LDL, and TG) will be determined via an enzymatic colorimetric method using commercial kits. Finally, the serum insulin concentrations will be examined using electrochemiluminescence (ECL) method. We also will determine insulin resistance (HOMA-IR) and quantitative insulin-sensitivity check index (QUICKI) formulas.

### Stool samples and gut microbiota assessment

A 10-g stool sample will be collected from each participant at study baseline, 3 months after intervention, and 6 months after the end of intervention using a stool specimen collection kit that will be brought to the clinic in ice packs within 4 h. Until fecal microbial analysis, stool samples will be frozen at – 80 °C in the laboratory. To minimize changes in the quantity of fecal bacteria, we will collect stool samples in one of three ways: first, we will invite patients to visit the laboratory on the day of fecal sampling. The lab will be equipped with all of the necessary equipment to collect fecal samples. The second method requires the patient to transport the sample to the laboratory within 4 h of their sampling. Finally, if the patient is unable to complete any of the prior approaches, they should contact the study researchers, who will collect their sample at their home and transfer it within 4 h to the lab.

DNA extraction from 200 mg of frozen stool samples will be done using a FavorPrep Stool DNA Isolation Mini Kit (Favorgen Biotech Corp., Taiwan) according to the manufacturer’s instructions. The extracted bacterial DNA purity and concentration will be determined by Nanodrop spectrophotometer (Thermo Scientific NanoDrop, USA). All the extracted DNAs will be stored at − 20 °C freezer until further analysis. Additionally, the quantity of fecal bacteria, including Firmicutes, Bacteroidetes, *Bifidobacteria*, *Lactobacillus*, *Clostridium*, *Prevotella*, *Bacteroidetes*, and *Akkermansia muciniphila*, will be determined using a quantitative real-time polymerase chain reaction (qRT-PCR) in duplicate. We selected the taxa based on their association with metabolic syndrome and their ability to balance the gut microbiota [39, 40]. Specific primers targeting the bacterial 16S rRNA genes blasted in NCBI will be used in the current study. Each reaction mixture is composed of SYBR Premix Ex Taq II (Takara, China), the specific forward and reverse primers, and a DNA template. The thermal cycling conditions will be as follows: an initial DNA denaturation step at 95 °C for 1 min, 40 cycles of denaturation at 95 °C for 5 s, primer annealing at 55 °C for 30 s, and extension at 72 °C for 30 s. Finally, in order to confirm the specificity of the amplification products, melting curve analysis will be performed by slowly cooling the PCRs from 95 °C to 60 °C.

### Anthropometric measures

Weight will be determined with the minimum clothing without shoes using a weighing calibrated scale (Seca, Hamburg, Germany) to the nearest 100 g. Standard stadiometer will be used to measure barefoot standing height to the nearest 0.5 cm. Measurement of the waist and hip circumferences will be done to the nearest 0.5 cm using a strip tape measure over light clothing without applying pressure to the body surface. The waist and hip circumferences will be defined as the circumference around the belly button and the diameter of the hip’s largest point. The body mass index (BMI) will be calculated by dividing weight in kilograms by the height in meters squared.

### Blood pressure assessment

After at least 5-min resting, measurements of systolic and diastolic blood pressure will be done twice with 15-min intervals in the right arm using a mercury barometer calibrated by the National Institute of Standards and Industrial Research. The average of two blood pressure readings will be used to determine an individual’s blood pressure.

### Physical activity assessment

We will determine the level of physical activity of participants based on their once in a month physical activity recording (including working and non-working days) (Supplementary file, section D). Physical activity levels will be classified as low, moderate, or high and expressed in metabolic equivalents per week (MET-min/week).

### Confidentiality

The information about participants will be stored anonymously according to TUMS rules. During laboratory tests and in all records, participants will only be able to be identified by their ID number so as to assure their privacy and confidentiality. In a secure database, we will store participants’ identifying information separately from the research data collected during the study. Moreover, all specimens will be stored in the TUMS biochemistry laboratory. All study data will be kept strictly confidential on password-protected computers in the research team’s office, which will be accessible only by the research team. The corresponding author will provide anonymized data to other researchers in order for them to conduct secondary studies after the trial has been completed on reasonable request.

### Statistical analysis

All statistical analyses will be carried out using the SPSS software version 25 (SPSS Inc., Chicago, IL, USA). For addressing non-adherence, the intention-to-treat (ITT) analysis will be applied [41]. Moreover, we will apply the last observation carried forward method (LOCF) to handle missing values [42]. In order to determine the normal distribution of variables, we will use the Kolmogorov-Smirnov test, histogram, and Q-Q plot. We will log transform (ln) the data, if necessary, to achieve normal distribution. Data will be presented as mean ± standard deviation (SD) for continuous variables and as percentages for categorical variables. Chi-square test and independent samples *t*-test will be used for comparing continuous and categorical variables between the two groups, respectively. We also will use the paired-sample *t* test for within-group comparisons. Repeated measures analysis of variance will be employed to determine the impact of the intervention on the outcome variables. These analyses will examine the effects of the intervention, time, and the interaction between time and intervention. Any potential differences in baseline levels of outcome variables, dietary intakes, and physical activity will be controlled in these analyses. Statistical significance will be defined as *P* values less than 0.05.

